**Discussion:**

The results of this trial will have a real impact on public health if it is shown that a Kenacort retard® (i.e. triamcinolone) injection costing just €2.84 and performed in the physician’s office (with no additional overhead costs) is at least as effective as the dexamethasone 700 μg implant (Ozurdex®; costing approximately €960 with the injection performed in a dedicated room), with no increased side effects.

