#### Treatment visit

At the beginning of the treatment visit (D0; injection of the product), the patient will answer their first EuroQol five dimensions (EQ-5D) questionnaire.

Before either the dexamethasone 700 μg implant or triamcinolone is injected, anaesthetic and antiseptic eye drops will be given according to the centre’s practices. Analgesics are permitted. Initiation of hypotensive eye drops for curative or preventive purposes is allowed. The investigator must report this in the case report form (CRF). According to the exclusion criteria, general anti-inflammatory treatments or systemic immunosuppressive or immunomodulatory treatments at unstable doses are not authorised during the trial. From D0, acetazolamide cannot be continued or introduced later.

For the subconjunctival triamcinolone injection (Kenacort retard®), the patient is positioned comfortably. The injection is performed after the instillation of anaesthetic drops. Triamcinolone injections are carried out using a 25-gauge needle. A volume of 0.4 ml is injected under the inferior bulbar conjunctiva so that the eyelid covers the visible crystals without discomfort.

For Ozurdex®, the injection is performed in the supine or semi-seated position. The eye is numbed with the instillation of anaesthetic eye drops. The eyelids and ocular surface are disinfected with antiseptic to reduce the risk of infection. The face is covered with a sterile drape and a sterile eyelid retractor is positioned. The injection device for the dexamethasone 700 μg implant is sterile and ready to use; it is inserted through the sclera 3.5 mm (pseudophakic eye) or 4 mm (phakic eye) from the lamina after moving the conjunctiva a few millimetres (Fig. 4). Following the injection, antibiotic eyedrops are instilled. The treated eye remains painless in the vast majority of cases. A spot may appear in the visual field, corresponding to the presence of the implant in the vitreous cavity (Fig. 2).

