For secondary end points, the mean visual analogue scale score evaluating the moment of injection will be compared between groups using a linear mixed model; the score for the moment (tolerable, uncomfortable or very unpleasant) will be compared using the Mantel–Haenszel stratified Chi-squared test. A linear mixed model will be used to compare the change in ETDRS from D0 to 6 months between the groups. SL and LFM between D0 and 2 months will be compared between the groups using nonparametric Van Elteren tests (semiquantitative outcome). Duration of injection efficacy (duration is determined by the reappearance of oedema) will be compared between the groups using the Van Elteren test (semiquantitative outcome). Descriptions of AEs/SAEs will be reported in the two groups. Comparisons between the groups will be performed using Chi-squared or Fisher tests for intermittent ocular hypertension, cataract, endophthalmitis, glycaemic and blood pressure imbalances in both arms. There will be no imputation for missing data for these secondary end points.

For the economic assessment, mean costs and their corresponding 95% CIs will be presented. The ICERs will be estimated along with their corresponding acceptability curves, i.e. the curves indicating the probability that an intervention is cost effective conditional on society’s willingness to pay for an additional unit of effectiveness (i.e. an additional QALY gained) and considering the sampling uncertainty around the estimated ICERs.

As costs and ICERs are not normally distributed, the 95% CI and the cost-effectiveness acceptability curves will be determined using the nonparametric bootstrap resampling technique.

Sensitivity analyses will be performed for all end points, adjusted for the duration of macular oedema. All statistical tests will be bilateral. For secondary endpoints, a *P* value less than 0.05 will be considered statistically significant. Analyses will be performed using SAS statistical software (SAS Institute Inc., Cary, NC, USA).

As this is a noninferiority study, the analyses will be carried out on the intent-to-treat population and on the per-protocol population. The intent-to-treat population consists of all randomised patients in the study. The per-protocol population includes the most compliant patients, based on compliance with the inclusion and exclusion criteria, absence of major deviations from the protocol and availability of the main criterion.

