#### Sample size

This TRIOZ trial aims to demonstrate the noninferiority of subconjunctival triamcinolone injections compared to intravitreal dexamethasone implants. Noninferiority will be evaluated in terms of the difference in macular thickness in the treated eye between D0 and M2. The deadline of M2 was chosen based on the plan for the Huron study on dexamethasone (NCT000333814) and a retrospective study on triamcinolone at CHU Nantes. Preliminary data observed retrospectively in Nantes between 2011 and 2013 in 25 patients who received triamcinolone injections showed a decrease of 0.12 ± 0.12 log OCT at M1 (D0, 0.27 ± 0.11; M1, 0.15 ± 0.08) and of 0.09 at M3 (0.18 ± 0.11). The difference in macular thickness between D0 and M2 is assumed to be the same in the two groups and the common standard deviation is set at 0.12. The noninferiority margin was set at 0.06, the power at 80% and the type I error rate at 2.5%. Based on these assumptions, 128 patients are needed to demonstrate the noninferiority of triamcinolone compared to dexamethasone. A maximum rate of 10% for missing data is taken into consideration for M2 and 142 patients, or 71 patients per group, will therefore be randomised in the study.

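### Difference tests at 71 per arm cannot support a claim of no increased side effects; report risk differences with confidence intervals and show pressure-lowering drop use by arm

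*Protocol article*

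**What the plan says.** The Discussion paragraph of the abstract makes the public-health impact conditional on triamcinolone being at least as effective as the implant "with no increased side effects". The closing paragraph of the Background and the main Discussion also present safety as part of the trial's question.

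Under Statistical methods, adverse events are described by arm and then: "Comparisons between the groups will be performed using Chi-squared or Fisher tests for intermittent ocular hypertension, cataract, endophthalmitis, glycaemic and blood pressure imbalances". Tests are two-sided, with significance at 0.05 for secondary endpoints. The article states no risk difference, confidence interval or margin for safety. The same section does use a confidence limit against a margin for macular thickness, and 95% intervals for costs.

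Under Sample size, the calculation uses macular thickness only: "128 patients are needed to demonstrate the noninferiority of triamcinolone compared to dexamethasone", and after allowance for missing data "142 patients, or 71 patients per group, will therefore be randomised in the study".

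On co-medication, the Treatment visit section says: "Initiation of hypotensive eye drops for curative or preventive purposes is allowed". It requires this use to be entered in the case report form. Study design says that assessments other than visual acuity and macular thickness cannot be masked.

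**The concern.** For efficacy, the plan recognises that showing a treatment is not worse requires a confidence limit judged against a margin. For safety, the conclusion the abstract looks for has the same logical form, but the stated method is a test for difference. A large P value from such a test may mean that the arms are alike or that the trial is too small to tell.

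The pressure comparison has a further weakness. Investigators know the allocation and may start pressure-lowering drops preventively. If they do so more often in one arm, fewer ocular hypertension events may be counted there, and the comparison as stated takes no account of it.

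At stake is the safety half of the comparison, in a trial whose authors hope it will support reimbursement of an off-label treatment.

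**Working it through.** **Inputs from the protocol article**
- Sample size: 71 per arm (64 before the missing-data allowance), margin 0.06, SD 0.12, true difference 0, one-sided 2.5%, power 80%.
- Background, rates for the implant: raised intraocular pressure 25.0% and cataract 11.8% in the pivotal uveitis study; elsewhere a rise above 10 mmHg in 15.4% to 27.7%, and cataract progression in 29.8% to 67.9%.

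**Assumptions made here:** these rates apply to the trial's own event definitions; true rates are equal when interval widths are computed; the alternative rates and the 10-point margin below are illustrative.

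**1. The plan's own figure.** n per arm = 2 × (1.96 + 0.84)² × 0.12² / 0.06² ≈ 62.8, so 63. With the t distribution, 64 per arm gives 80.1% power (63 gives 79.5%), so 128 in total. 128 / 0.9 = 142.2, in line with 142. The sample size reproduces, and no safety event enters it.

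**2. Interval width at 71 per arm.** Half-width = 1.96 × √(2p(1 − p)/71).

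| Event and rate p | Half-width (points) |
|---|---|
| Raised pressure 25.0% | 14.2 |
| Pressure rise 15.4% | 11.9 |
| Pressure rise 27.7% | 14.7 |
| Cataract 11.8% | 10.6 |
| Cataract 29.8% | 15.0 |
| Cataract 67.9% | 15.4 |

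With 64 per arm, the first figure becomes 15.0 and the 11.8% cataract figure 11.2.

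**3. Power of the stated tests** (two-sided 0.05; normal approximation with pooled null variance, exact Fisher beside it).
- 25% versus 35%: null standard error √(2 × 0.30 × 0.70/71) = 0.0769; alternative √((0.1875 + 0.2275)/71) = 0.0765; z = (0.10 − 1.96 × 0.0769)/0.0765 = −0.66. Power is 25% (Fisher 20%).
- 25% versus 40%: 48% (Fisher 41%).
- 11.8% versus 21.8%: 36% (Fisher 29%).
- 80% power against 25% is reached only at about 47.5%, and against 11.8% only at about 31%.

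**4. What a non-significant result leaves open.** Take 28/71 versus 18/71 (39% versus 25%, a 14-point excess). Chi-squared P = 0.073, with a Newcombe 95% interval of −1.3 to +28.6 points. Even identical counts, 18/71 in each arm, give −14.2 to +14.2.

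**5. What excluding an increase would need.** To rule out an assumed 10-point increase with 80% power at one-sided 2.5%: 7.85 × 2 × 0.25 × 0.75 / 0.10² ≈ 295 per arm at 25%, and 164 per arm at 11.8%, against 71 planned.

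**6. Drops, illustration only.** Suppose true rates of 40% and 25%, and drops that avert a quarter of events in the first arm alone. The observed contrast becomes 30% versus 25%, and power falls from 48% to about 10%. The document gives no figure for unequal use, and use concentrated in the other arm would widen the contrast.

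**The case against.** A reader might infer that the plan will declare no increase whenever P exceeds 0.05. The document does not say so. The phrase appears once, in a conditional remark in the abstract; the parallel cost argument in the Background has no safety clause; and the only formal noninferiority claim concerns macular thickness. What stands is narrower: these tests are the only safety inference stated, so a null result could be read in that way.

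A reader might also infer that preventive drops will hide a pressure signal. That needs unequal use between arms, for which the document gives neither rate nor direction. Drop use is recorded, concomitant medication is noted at follow-up, and pressure is measured monthly, so the matter can be examined. The article does not define ocular hypertension as an event, and the full protocol or analysis plan may already address treatment initiation.

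Low power for secondary safety events is normal in a trial sized on efficacy and is not a design error. Intervals beside a test are often left to the analysis plan, which is not shown. That limits the weight of the point but does not remove it, because the article names a method, and that method cannot carry the claim in the abstract.

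Endophthalmitis adds little. Zero events in 71 gives an upper limit of 5.1% (1 − 0.025^(1/71)), but this is a bound for one arm, not for an increase between arms, and the main Discussion attributes that risk to the intraocular device.

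On cataract, the Treatment visit section provides for pseudophakic eyes, so fewer than 71 per arm are likely to be at risk. That makes the intervals wider than shown.

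**Conclusion.** The point holds as a mismatch between the claim the article looks for and the safety inference it states. At 71 per arm, a non-significant result would be compatible with increases of about 12 to 15 points in raised pressure over the cited rates even if the observed rates were equal, and with more if triamcinolone's were higher. For cataract the figure is about 11 points at 11.8% and about 15 points at the higher rates cited. Power for an assumed 10-point increase in raised pressure from 25% is about 25%.

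These sizes rest on the cited implant rates carrying over to this trial's definitions and population. The direction of the conclusion does not depend on the exact rate within the cited ranges. The drops issue is a possible, unquantified attenuation under open allocation, not a demonstrated bias.

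This is an inexpensive improvement to analysis and reporting. It does not touch the primary comparison.

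**What to change.** - For each listed event, report the risk difference (triamcinolone minus dexamethasone) with its 95% confidence interval beside the Chi-squared or Fisher result.
- Allow wording about no increase only as a statement of the upper limit, for example the largest increase the data do not exclude; otherwise drop it.
- Tabulate initiation of pressure-lowering drops by arm from the case report form, separating curative from preventive use where this was recorded.
- Keep the ocular hypertension comparison unmodified, and add a sensitivity analysis that counts initiation of drops as an event.

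The cost is analysis-plan wording; no further patients or visits are needed, and drop use is already recorded. The safety claim becomes more modest. The sensitivity analysis may be inflated by discretionary prophylaxis, possibly unequally by arm, which is why both versions should be shown. No change to clinical management is proposed.

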#### Measures used to determine the outcomes

OCT is used to accurately visualise the different layers of the retina, including the macula, using an infrared laser. This is a contactless examination which is noninvasive, painless and brief.

An LFM is a device used to measure the protein concentration in the anterior chamber using a helium–neon laser. This is a contactless examination that is non-invasive, painless and brief.

All the ophthalmic examinations performed at inclusion and during follow-up are common practice in ophthalmology. The visual acuity, IOP, examination using the SL and fundus examination form the basis of all clinical ophthalmic examinations. OCT is the test of choice for characterising and quantifying macular oedema, irrespective of type. This testing is contactless and is noninvasive, painless and brief. The values considered to be normal are: visual acuity, ETDRS 100; IOP, 12–21 mmHg; LFM, no proteinic flare or cellular Tyndall; fundus, no cellular Tyndall or vitreous haze; macula as described, normally LFM <10 ph/ms, CMT <300 μm and >250 μm.

The patient will be given the EQ-5D questionnaire validated in France [28, 29] at each visit to measure their quality of life. The EQ-5D consists of a questionnaire and a visual analogue scale. The questionnaire focuses on five areas: mobility, personal autonomy, current activities, pain/discomfort and anxiety/depression. There are three possible answers for each of these dimensions (EQ-5D-3 L), thus allowing for 243 health states. QALYs will be calculated for each arm using area under the curve methodology and the weighting coefficients available in France for the EQ-5D-3 L [29, 30].

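### The bootstrap sentence can be read as putting a 95% CI on the ICER, and that interval would be unreadable if the QALY difference is close to zero

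*Protocol article*

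**What the plan says.** All references are to the Protocol article.

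- **Efficiency outcomes** names one measure: the ICER, as cost per QALY, over six months and from society's standpoint.
- **Measures used to determine the outcomes** adds that "QALYs will be calculated for each arm using area under the curve methodology", with French EQ-5D-3L weights. The EQ-5D is completed at D0 before the injection (Treatment visit) and at each monthly visit to M6 (Follow-up visits).
- **Statistical methods** makes three statements in order. Mean costs will be shown with 95% CIs. ICERs will be shown with acceptability curves. Then: "As costs and ICERs are not normally distributed, the 95% CI and the cost-effectiveness acceptability curves will be determined using the nonparametric bootstrap" resampling technique.
- **Background** gives unit prices of EUR 2.84 for triamcinolone and EUR 962.65 for the dexamethasone implant. It also reports a retrospective study of 88 patients from the same department that found no difference between treatments.
- **Sample size** states that "The difference in macular thickness between D0 and M2 is assumed to be the same in the two groups". This concerns macular thickness, not QALYs.

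**The concern.** The ICER is the cost difference divided by the QALY difference. If the test treatment is cheaper and the QALY difference is near zero, some bootstrap replicates have a small positive denominator and others a small negative one. The ratio then jumps from a very large negative value (cheaper and slightly better) to a very large positive one (cheaper and slightly worse). These two outcomes are neighbours on the cost-effectiveness plane but lie at opposite ends of the number line. Sorting the replicates and taking the 2.5th and 97.5th percentiles does not give a range of plausible values.

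The design makes this a realistic risk: a noninferiority comparison, a large price gap, a short horizon, and earlier data from the department showing no difference. Cost is also central to the article's policy case (abstract Discussion, Background, Discussion), so an ICER interval, if reported, would be read closely.

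**Working it through.** **1. The plan's own figure.** The article gives no economic figure to reproduce. The primary sample size does reproduce.

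- Inputs: "The noninferiority margin was set at 0.06, the power at 80% and the type I error rate at 2.5" per cent, and "the common standard deviation is set at 0.12".
- Normal approximation: n per arm = 2 × (1.96 + 0.84)² × 0.12² / 0.06² = 62.8, so 63 per arm and 126 in total. With the noncentral t distribution it is 64 per arm, 128 in total, power 0.801. The article says "128 patients are needed to demonstrate the noninferiority of triamcinolone compared to dexamethasone".
- Attrition: "A maximum rate of 10% for missing data is taken into consideration for M2", and 128 / 0.9 = 142.2. The article says "142 patients, or 71 patients per group, will therefore be randomised in the study".

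The primary sizing is sound and is not touched by this point. The economic comparison therefore has 71 patients per arm.

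**2. Does the text put a CI on the ICER?** For: the stated reason for bootstrapping the interval is the non-normality of both costs and ICERs. Against: the two preceding sentences attach CIs to costs and acceptability curves to ICERs. The sentence is ambiguous.

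**3. How would a percentile interval for the ICER behave?**

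- From the article: 71 per arm; price difference 2.84 - 962.65 = -EUR 959.81.
- Assumed, because the article gives none: six-month QALY SD 0.05, 0.08 or 0.12; other costs with SD EUR 600 and the same distribution in both arms; costs independent of QALYs.
- SE of the QALY difference = SD × √(2/71): 0.0084, 0.0134 and 0.0201.
- Simulation: 200 trials per scenario with 1,000 resamples each. A trial counts as spanning zero when between 2.5% and 97.5% of its replicates have a positive QALY difference.

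| True QALY difference | SD 0.05 | SD 0.08 | SD 0.12 |
|---|---|---|---|
| 0 | 94% | 96% | 93% |
| 0.01 | 78% | 89% | 91% |
| 0.02 | 35% | 64% | 81% |
| -0.02 | 34% | 66% | 82% |

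Hand check of one cell (0.01, SD 0.05): 0.01 / 0.0084 = 1.19, and Φ(1.96 - 1.19) - Φ(-1.96 - 1.19) = 0.78, which agrees.

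At a true difference of zero, the median percentile limits for the ICER were, in EUR per QALY:

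- SD 0.05: -1,333,000 to +1,349,000
- SD 0.08: -868,000 to +873,000
- SD 0.12: -536,000 to +545,000

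These limits are set by the replicates with the smallest QALY differences. For SD 0.05, 959.81 / 1,333,000 = 0.0007. The interval therefore cuts off the replicates nearest to no QALY difference, which is the opposite of what a CI should do.

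**4. Does an alternative stay readable?** Incremental net monetary benefit = λ × QALY difference - cost difference. Take an assumed λ of EUR 30,000 and an observed QALY difference of 0. The 95% CI is 959.81 ± 1.96 × √[(30,000 × SE)² + (600 × √(2/71))²].

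- SD 0.05: EUR 428 to 1,491; probability cost-effective about 1.00
- SD 0.08: EUR 146 to 1,774; 0.99
- SD 0.12: EUR -241 to 2,160; 0.94

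**5. Baseline EQ-5D, a separate matter of precision.** With an assumed utility SD of 0.15 to 0.25, a one-SE chance imbalance at D0 is SD × √(2/71) = 0.025 to 0.042. If a fraction b of 0.5 to 1.0 carries through the half-year, the QALY difference shifts by 0.5 × b × imbalance, that is 0.006 to 0.021. Adjustment reduces the variance by ρ², which is 16% to 36% for an assumed correlation of 0.4 to 0.6.

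**The case against.** The strongest reply is that the article never clearly promises a CI for the ICER. Read in order, costs take the interval and ICERs take the curve. That reading is tenable, and it is why this is a request to clarify and not an established error. It does not remove the point: the bootstrap sentence names ICERs as a reason for the interval, and the article states no interval for the QALY difference or for net benefit.

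A second reply is that the acceptability curve already expresses the uncertainty. This stands. At each willingness to pay, the curve is the probability that net benefit is positive, and it is well defined when the QALY difference is near zero. A reader might infer that the whole economic result is uninterpretable; the article does not support that. What the curve lacks is the size of the benefit with an interval.

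A third reply is that no near-zero QALY difference is stated. This also stands. The equality assumption in Sample size is for macular thickness to M2. Six-month QALYs may also reflect adverse events and the treatment that investigators may choose after M3. Nor do half of the replicates take each sign whenever the true difference is zero. Replicates centre on the observed difference, so an even split holds only on average or when the observed difference is zero.

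Finally, a reader might infer from the area-under-the-curve sentence that QALYs will be left unadjusted for baseline. The article neither says so nor excludes adjustment, and such detail is commonly left to an analysis plan. Lack of adjustment would in any case affect precision and chance imbalance; it is not what makes a ratio interval unreadable.

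**Conclusion.** The point holds conditionally. If the bootstrapped 95% CI is meant to cover the ICER, it would often fail to be an ordered range. At a true QALY difference of zero, 93% to 96% of simulated trials span zero. At 0.01 it is 78% to 91%, and at 0.02 in either direction 34% to 82%. A clear QALY difference with a small SD would largely remove the problem.

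These sizes rest on assumed SDs for QALYs and other costs, and on taking the drug price gap as the expected cost difference. That the true difference may be small is an inference from the noninferiority design, the price gap and the department's retrospective study. Only an ICER interval is affected. The acceptability curve, the primary analysis and the sample size stand. It is a minor point on a secondary analysis.

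**What to change.** In the economic paragraph of Statistical methods, or in the analysis plan:

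- State what the 95% CI covers, and that no percentile CI will be given for the ICER when bootstrap replicates cross quadrants.
- Report incremental cost and incremental QALYs, each with a bootstrap 95% CI.
- Report incremental net monetary benefit with its 95% CI over a range of willingness-to-pay values, beside the acceptability curve.
- As a separate gain in precision, estimate the QALY difference within each replicate by regression on arm and D0 EQ-5D.

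The cost is a few sentences and a few lines of code. The same replicates serve every output, the D0 EQ-5D is already collected, and no new data are needed.
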